## 6.2 Data:

Information about participants' demographic, anthropometrics, medical conditions, medication use, and dietary patterns will be collected, in addition to stool, urine, and blood samples. Participant samples will be stored and analyzed by unique study identification numbers only. Only the study team has the link between samples and individual participants and linkage will not be released outside of this trial. Study data will be presented and published only in ways that make it impossible to identify individual participants.

## 6.3 Release/Sharing:

For participants who agreed to have their samples used for future research, these samples may be shared for that purpose with outside collaborators at the investigator's discretion, with input from Hmong Gout Coalition members, only after appropriate regulatory approval has been given, and a material transfer agreement is in place.

## **7.0 Sharing of Results with Participants**

7.1 Participants will receive individual results including vital signs, anthropometry, renal function, serum urate level, COVID19 antibodies, genetics, and microbiome results. We will also share the aggregated genetics and microbiome results with participants. However, we will stress that analysis of biological samples is for research purposes only and are not necessary for participants' clinical care.

7.2 Sharing of genetic testing:

7.2.1 Disclosure of results:

Selected individual and aggregated genetic testing results will be returned to participants. We are only analyzing specific genes related to HU, gout and medicines commonly used to treat gout. Although genes related to response to other medications may be examined, we are not testing for genes associated with other diseases, for example those associated with risks for cancer, seizures, or psychiatric diseases; we will not report any incidental findings, including genetic relationships (relatedness) between people. In addition, genetic testing will be conducted in a research lab instead of in a lab certified under Clinical Laboratory Improvement Amendments (CLIA) and consequently we are recommending any result be not considered for interpretation in a clinical situation.

7.2.2 If returning results to participants:

- Aggregate or individual results:  
Participants will receive both individual and aggregated results. Aggregate results will be presented in a way that does not allow participants to see other participants' genotypes.
- Laboratory results:  
The genetic testing will be conducted in a research laboratory instead of a lab certified under Clinical Laboratory Improvement Amendments (CLIA). Participants will be informed that the results are for research use only and should not be used for routine clinical care. Contact information for a CLIA laboratory will be provided (such as UMMC Molecular Diagnostic Laboratory) if the participants choose to confirm the results. However, participants will have to pay for this clinical information.
- Plan for return of results to participants:

Aggregated results will be shared at the conclusion of the study with the participants and the Hmong community at several venues and through several media. These may include locations, such as recruitment sites, community conferences, community events, community organizations and media including Hmong radio and television, and the Hmong Gout Coalition website. In addition, we will share results with local physicians and pharmacists who have partnered with recruitment, and we will disseminate our results with broader audiences by presenting at local, national, and international conferences, and by publishing peer-reviewed articles in scientific journals.

Individual participant results will also be shared at the conclusion of the study. We will mail relevant individual results to the participants. Since the genetic results will not affect routine clinical care, credentialed genetic professionals will not be used to explain study results in-person.

- Types of results to be returned to participants:
  - a . Personal anthropometry and vital signs
  - b . Personal blood test results: SU before and after Vitamin C
  - c . Personal microbiome results: Summary of microbiome results, before and after vitamin C, and any correlations with trigger foods
  - d . Personal genetic results\*\*: We will only be returning genetic variants on genes which have been shown to be associated with urate absorption and reuptake, including *ABCG2* and *SLC22A12*.
  - e . Personal SARS-CoV-2 antibody test results

\*\*There is still a lack of evidence or consensus supporting the clinical interpretation of these genetic variants and microbiomes and their impact on HU/gout and or response to drug therapy. This therefore limits any important interpretation. However, since the Hmong community has consistently expressed their desire to receive information on their results, we have agreed to provide our research findings or select data above, noting they are of limited, if of any, clinical value. There will be no concerns with incidental findings because we are only looking for genetic variants that are associated with the treatment efficacy and not disease-causing genetic variations.

#### 7.2.3 Future analysis of genotypes:

The research team will offer the participants options for future use of their de-identified DNA material, which they will indicate on their consent form, including

their permission for: our research team or other research teams to analyze their DNA for any future research study; or our research team or other research teams to analyze their DNA only for future research studies about genes and medicines without contacting them; or their permission for us to contact them about possible future studies.

For participants consenting for further analysis of the significance of genotypes in the future, the research team may conduct additional studies to examine the impact of genetic variants on the risk of HU and gout or other related research questions, with IRB permission. In such cases, additional IRB approval will be sought.

## 8.0 Study Population

### 8.1 Inclusion Criteria:

- Self-identified Hmong men and women whose both parents are Hmong,  $\geq 18$  years of age, with and without hyperuricemia (serum urate  $\geq 6.8$  mg/dL) and/or gout (defined by 2020 Gout Classification Criteria defined by American College of Rheumatology) are eligible for the study
- Willing and able to provide informed consent
- Willing and able to adhere to the study protocol

**Gout group:** Individuals with hyperuricemia and/or gout are defined as:

- serum UA  $\geq 6.8$ mg/dL based on the baseline measurement (with or without stable ULT\*)
- serum UA  $< 6.8$  mg/dL based on the baseline measurement (with or without ULT) with at least 1 episode of peripheral joint or bursal swelling, pain, or tenderness (acute gout flare) in their lifetime

\*ULT= Urate Lowering Therapy, includes allopurinol, febuxostat, probenecid, lesinurad, and benzbromarone

**Non-gout group:** Individuals without gout, without ULT, and with serum UA  $< 6.8$  mg/dL. Individuals who are siblings or other family members to those with gout are allowed

### 8.2 Exclusion Criteria:

Participants with following conditions will be excluded from the study:

- Allergy or sensitivity to vitamin C
- Diagnosis/history of:
  - Gastrointestinal surgery including colectomy, ileectomy, and gastrectomy
  - Inflammatory bowel disease

- Auto-immune disease
- Type I diabetes mellitus
- Severe kidney disease (i.e., on dialysis)
- End-stage liver disease (i.e. cirrhosis)
- Pregnant women
- Breastfeeding women
- Glucose-6-phosphate dehydrogenase deficiency (due to increased bleeding risk in patients with G6PD deficiency when receiving vitamin C)
- Current use of:
  - Antibiotics
  - Probiotics supplement
  - Ketogenic diet

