## 2.0 Background

Gout, caused by chronic elevation of serum urate (SU), is the most common form of inflammatory arthritis worldwide. About 3.9% of adults in the U.S. suffer from gout and prevalence is even higher in certain ethnicities. Factors that may influence SU include patients' characteristics (gender, weight, renal function, etc.), genetics, and diet. Foods and beverages that have shown positive association with HU and gout are alcohol (particularly beer), purine-rich foods, red meat, seafood, and sugar-sweetened drinks, while inverse association has been found with dairy intake such as skimmed milk and low-calorie yoghurt, coffee and vitamin C.

The gut microbiota composition and function have been linked to common chronic human disorders, such as obesity, diabetes, non-alcoholic fatty liver disease, and rheumatoid arthritis. Intestinal microbiota of gout patients were also found highly distinct from healthy individuals in both organismal and functional structures from a small study conducted in China. Strategies to use personal microbiome features to predict glucose response to specific food have been proposed. However, **little is known about the impact of microbiota on food and urate-lowering therapy (ULT)**. The translational significance of a microbiota-guided approach to select appropriate foods and medications that could prevent the elevation of SU for individuals with gout or at high risk for gout is significant.

The Hmong are a unique Asian sub-population. Hmong men exhibit a 2-fold higher prevalence of gout, manifesting it earlier in life and experiencing up to 5-fold increased risk of gout-associated complications, compared to non-Hmong in the US. This could lead to higher rates of cardiometabolic diseases (e.g. hypertension, renal disease, type 2 diabetes [T2DM]), which significantly impact morbidity, mortality and healthcare costs. To prevent acute gout attack and reduce complications associated with gout and/or HU, it is critical to maintain UA below 6 mg/dL.

In this study, we will test four hypotheses and thereby accomplish our objectives as following:

**Ho (1):** High dose vitamin C intervention improves outcomes in (a) healthy adults and (b) patients with HU and/or gout.

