### **4.0 Study Intervention(s)/Investigational Agent(s)**

4.1 Description:

All participants will be taking vitamin C 500 mg twice daily by mouth for 8 weeks. All participants will continue taking their prescribed medications during the study period.

Vitamin C is commercially available over-the-counter food supplements. Vitamin C will be purchased from a GMP manufacturer (such as Pure Encapsulations, Sudbury, MA) which can demonstrate a good quality and safety of the product.

4.2 Drug/Device Handling:

The vitamin C will be stored securely in a locked cabinet at [name] office. Vitamin C is an over-the-counter product and will be distributed by research staff as per applicable regulations. The label will list the name of the study, the number and frequency of tablets to be taken, the participant's name and ID number, and the phone number for a pharmacy helpline. A study dispensing and accountability log will be maintained by bilingual research staff. The participants will be reminded to return the study pill containers and any remaining tablets at Week 8.

- 4.3 Biosafety: This study does NOT involve recombinant or synthetic nucleic acid molecules (r/sNA; RNA, DNA), infectious agents, or biologically-derived toxins.
- 4.4 Stem Cells: This study does NOT involve embryos or embryonic stem cells.
- 4.5 Fetal Tissue: This study does NOT involve human fetal tissue or cell lines derived from human fetal tissue.

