### 5.2 Study Procedures:

**Recruitment process:** Our recruitment and enrollment plan in the Minneapolis/St. Paul MN metropolitan area includes outreach, electronic, print, and social media to ensure we can enroll 180 participants to reach statistical power. (*Recruitment flyers and scripts uploaded as supplements.*) Depending on COVID-19 restrictions during enrollment, we are planning on collecting data either together in person with a research staff (which can happen at a clinic, another location of their choice, or at their home), or separately with the participants collecting data in their home, with research staff supporting them remotely by phone or by Zoom, as participants prefer.

**Enrollment visit (Visit 1):** The enrollment visit will take approximately 120 minutes. During the visit, bilingual (English and Hmong) researchers will review and discuss the study, consent form, and HIPAA form in participants' preferred language. Any questions will be answered, and the researcher will assess if potential participants understand what is expected of them before they sign the consent and HIPAA forms.

Once the consent form is signed, participants will complete questionnaires about their medical history, gout symptoms, lifestyle activities (including diet and tobacco, and exercise) and medication history (including prescription, over-the-counter medications, probiotics and herbal therapies). Researchers will measure anthropometry (height, weight, and waist- circumference), and vital signs (temperature, respiratory rate, oxygen saturation, blood pressure and heart rate).

**Trigger-food profiling:** Researchers will ask participants to identify their gout flare trigger foods, first by an open-ended question and then by reviewing a list of common trigger foods, developed with a Hmong registered dietician. We will ask if there is any known "amount" (dose) of the trigger food known to them and have them grade them as the "highest, moderate or lowest" association with triggering gout in them.

**Medication history:** Participants may be asked to bring their medications with them to the enrollment visit and may be asked about their adherence to these medicines. If

necessary, the researchers will ask for permission to get a current medication list from their medical clinic.

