**21.3 Waiver of Written/Signed Documentation of Consent (when written/signed consent will not be obtained):**

The intervention of the study is vitamin C at the typical over-the-counter dose. The biological samples (blood in an amount of no more than 3 ml per kg in an eight-week period, saliva, urine, and stool) collected in the study are no more than minimal risk. Since only adults will be enrolled in the study, no newborn dried blood spots will be collected. Paper or electronic HIPAA form and consent form will be provided to all participants according to the procedure described in the consent process.

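### Section 8.2 does not exclude current vitamin C users, so some baseline urate values may already reflect the study agent and pull the mean change toward zero

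*Protocol*

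**What the plan says.** Section 8.2 introduces the exclusions with "Participants with following conditions will be excluded from the study". The items under current use are antibiotics, "Probiotics supplement" and ketogenic diet. Vitamin C itself is a reason for exclusion only as "Allergy or sensitivity to vitamin C"; it is also mentioned in the rationale for excluding G6PD deficiency. The inclusion criteria and group definitions in Section 8.1 do not mention it. No section sets a washout, tells participants to stop their own vitamin C, or stratifies by earlier use.

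Section 4.1 states "All participants will be taking vitamin C 500 mg twice daily by mouth for 8 weeks" and "Vitamin C is commercially available over-the-counter food supplements". It says that prescribed medicines continue and is silent on a participant's own supplements. Section 21.3 adds: "The intervention of the study is vitamin C at the typical over-the-counter dose". Section 2.0 lists dietary factors linked to hyperuricemia and gout, "while inverse association has been found with dairy intake such as skimmed milk and low-calorie yoghurt, coffee and vitamin C".

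Section 3.1 makes the absolute change in serum urate after 8 weeks the primary endpoint. At Visit 1, Section 5.2 records "medication history (including prescription, over-the-counter medications, probiotics and herbal therapies". Section 15.3 adjusts the urate change for concomitant medications, among other covariates.

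**The concern.** The study is open-label and has no untreated arm. The effect of vitamin C under Ho1 is therefore read entirely from each person's change since baseline. That reading assumes a baseline free of the study agent, and the eligibility criteria do not secure this.

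The protocol's own description makes earlier use plausible. The agent is sold without prescription, and the study dose is called typical of such use. Someone already taking a similar amount enters with a urate level that may already be lowered, and can be expected to show a smaller further fall whether the study tablets replace the supplement or come on top of it. The mean change then mixes the effect of starting vitamin C with the effect of continuing or adding to it. No control group reveals or cancels the difference. What is at stake is an underestimate of the effect and a loss of power against the 0.5 mg/dL that the sample size assumes.

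**Working it through.** **Inputs (Section 15.2).** Fall of 0.5 mg/dL; one-sided t-test; type 1 error 0.01; power 80%; drop-out 15%; 120 adults with HU and/or gout (SD 1.5 mg/dL) and 60 without (SD 1.0 mg/dL). Completers: 0.85 × 120 = 102 and 0.85 × 60 = 51.

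**The plan's own figure.** A one-sample t-test on the change (noncentral t) needs 94 and 43 completers. Dividing by 0.85 gives 110.6 and 50.6, so 111 and 51 enrolled. The stated 120 and 60 are not reproduced, but they are larger than needed, so there is some slack. At 102 and 51 completers the noncentrality d√n/SD is 0.5 × √102 / 1.5 = 3.37 and 0.5 × √51 / 1.0 = 3.57. Power is 84.0% and 87.4%.

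**Dilution.** Let f be the share already using vitamin C and r the fraction of the effect that they still gain. The mean fall is

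d = 0.5 × [(1 − f) + r × f].

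Both f and r are assumptions, because the protocol gives neither. Two cases are shown: r = 0 (no further gain, the worst of the two) and r = 0.5 (half the effect). SDs are kept at the plan's values.

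| f | r | Mean fall, mg/dL | Power, HU/gout (102) | Power, no HU/gout (51) |
|---|---|---|---|---|
| 0% | – | 0.500 | 84.0% | 87.4% |
| 5% | 0 | 0.475 | 79.6% | 83.5% |
| 10% | 0 | 0.450 | 74.6% | 78.8% |
| 20% | 0 | 0.400 | 63.0% | 67.5% |
| 30% | 0 | 0.350 | 49.9% | 54.2% |
| 10% | 0.5 | 0.475 | 79.6% | 83.5% |
| 20% | 0.5 | 0.450 | 74.6% | 78.8% |
| 30% | 0.5 | 0.425 | 69.0% | 73.4% |

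Mixing users and non-users also widens the spread: f(1 − f) × [0.5(1 − r)]² is added to the variance. This changes little. At f = 20% and r = 0 power becomes 62.1% and 65.5%; at f = 30% and r = 0.5 it becomes 68.7% and 72.8%.

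**Reading.** The slack in 120 and 60 is used up quickly. In the HU/gout group power drops just below 80% at about 5% users if they gain nothing, or about 10% if they gain half. In the group without HU or gout the crossing lies between 5% and 10% with no gain, and between 10% and 20% with half the gain.

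**The case against.** The strongest reply is that users can be identified. Over-the-counter medicines are recorded at Visit 1, medication and dietary history is repeated at Visit 2, and the regression in Section 15.3 adjusts for concomitant medications, a term not limited to prescribed drugs. A reader might infer from the missing exclusion that users cannot be separated from non-users afterwards. The protocol does not support that: the recorded history permits an analysis in non-users. What stands against the reply is that Section 15.3 does not name supplements, and that separating users afterwards neither restores an untreated baseline nor undoes the dilution of the overall mean.

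A second reply is that the size is hypothetical. This stands. Over-the-counter availability and a typical dose show that earlier use is possible, not that it is common in this community. A supplement user is also not necessarily on the study regimen: someone taking a low-dose multivitamin could still respond to 500 mg twice daily. That is why the half-gain case belongs beside the no-gain case.

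Third, this error makes the effect look smaller and does not create one, and admitting users could be defended as studying an unselected community. Both points are fair and lower the weight of the finding. They do not remove the bias in an estimate meant to quantify what vitamin C does.

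A reader might also infer that the before-after microbiome comparison is diluted in the same way. The protocol gives no microbiome effect size or dose response for vitamin C, so that is not claimed here.

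**Conclusion.** The point holds as a cheap improvement to eligibility. Current vitamin C users are eligible, no washout is set, and baseline is the sole comparator, so any such users are expected to pull the mean urate change toward zero.

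The direction follows from the design; the size rests on assumptions. For assumed shares of 10% to 30%, power falls from 84% to about 75% to 50% in the HU/gout group and from 87% to about 79% to 54% in the other group if users gain nothing further. If they gain half the effect, it falls to about 80% to 69% and 83% to 73%. With few users or a good residual response the loss is marginal. The trial remains interpretable, and the conclusion does not extend to the microbiome outcomes.

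**What to change.** Add current vitamin C supplement use to the current-use items in Section 8.2, and add a matching question to the telephone eligibility assessment in Section 8.3. Whether to set a content threshold (for multivitamins, say) or a washout, and at what level or length, is for the investigators.

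For participants already enrolled, flag baseline use from the over-the-counter history taken at Visit 1 and pre-specify a sensitivity estimate for Ho1 in non-users. Keep all enrolled participants as the primary analysis: removing users from it now would redefine the primary population midway through an open-label study.

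The cost is one eligibility line, one screening question and one extra analysis, with a slightly smaller recruitment pool.

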### **3.0 Study Endpoints/Events/Outcomes**

3.1 Primary Endpoint/Event/Outcome: Absolute change in serum urate after the 8 week of vitamin C intervention

3.2 Secondary Endpoint(s)/Event(s)/Outcome(s): Secondary outcomes include the followings:

- Change in gout related symptoms measured by Gout Assessment Questionnaire 2.0^15 and number of joints affected by gout using Swollen Joint Count (44 Joints) post-administration of vitamin C
- Change in BMI
- Taxonomic and functional patterns of gut microbiota associated with SU
- Change in taxonomic and functional patterns of gut microbiota post-administration of vitamin C
- Taxonomic and functional patterns of gut microbiota associated with food types that trigger gout

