## 5.0 Procedures Involved

- 5.1 Study Design: This is an open-label interventional study. We aim to enroll 2:1 matching between participants with HU and/ or gout and participants without HU and gout. We aim to have 3 analysis groups of about 60 people per group (total about 180 participants): 1) people with HU or gout with ULT, 2) people with HU or gout without ULT, 3) people without HU or gout without ULT.

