Gout Symptoms: The modified Gout Assessment Questionnaire 2.0^23 (modified by a cultural equivalent approach) and Swollen Joint Count (44 Joints) ([https://www.carearthritis.com/tools/tools\\_html.anonlaunch?toolid=8&refid=/physicians.php%23tab2](https://www.carearthritis.com/tools/tools_html.anonlaunch?toolid=8&refid=/physicians.php%23tab2) ) will be used.

Stool collection: Participants will be instructed in stool collection and will be given stool collection kits to take home with them for 2 consecutive days. They will return the samples at their convenience. Upon receipt at the study lab, the samples will be stored at -80°C until DNA extraction.

Blood collection: We will be offering two methods: 1) in person and 2) at home method. In person blood draws will be performed by a phlebotomist available at the visit and later for subjects who are not ready to consent at the visit but choose to consent later. Blood samples will be collected into serum collection tubes (BD 366668-1 Vacutainer® Plus Plastic Serum Blood Collection Tubes or equivalent) and stored at -20°C until testing. For at home blood collection, capillary blood collection tubes (Microvette® CB 200 uL or equivalent) will be available to participants for self-collection. After self-collection, participants will ship samples to [name]'s lab according to the regulation of Occupational Safety and Health Administration (OHSA) and Department of Transportation (DOT) to and stored at -20°C until testing.

We will test for serum urate and creatinine to assess kidney function (calculate eGFR), which is a confounding contributor to SU. Inflammatory markers link to gout and obesity will also be tested.

Viral serology (antibody test) related to SARS-CoV-2 will be tested using the method developed and validated at the Advanced Research and Diagnostic Laboratory (ARDL), University of Minnesota.

Saliva collection: DNA will be extracted from the saliva samples collected using a commercial collection kit. Genetic variants that are associated with HU, gout, the responses of ULT, or other medications which the participants may be taking during the study will be tested. Although others may be examined as this field of study evolves, some known examples of genes that will be assessed for genetic variations that impact either medications used or the conditions of HU and/or gout include *ABCG2*, and *SLC22A12*.

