#### 15.3 Statistical Analysis:

Absolute SU changes from baseline to week 8 will be calculated using multiple linear regression adjusting for patients' characteristics including age, gender, BMI, renal function, and concomitant medications. Genetic variants and microbiome features will be tested with forward stepwise regression.

Overall differences in microbiome composition from baseline to week 8 will be compared using three principle axes of variation in the microbiome. A linear regression will be analyzed with a bacterial taxon as dependent and host factors as independent variables. The significance of association of a host factor will be determined by the test of the null hypothesis that the coefficient is equal to zero. For microbiome features, we will correct computed p-values for the total number of comparisons between dependent and independent variables using false discovery rate correction.

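### Section 8.2 excludes only current antibiotic and probiotic use, so recovery from a recently finished course can be mistaken for a vitamin C effect on the microbiome

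*Protocol*

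**What the plan says.** Protocol section 8.2 lists antibiotics, probiotic supplements and a ketogenic diet under "Current use of". It gives no look-back or washout, and antibiotics are not mentioned anywhere else in the protocol.

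Section 4.1 gives everyone the intervention: "All participants will be taking vitamin C 500 mg twice daily by mouth for 8 weeks". Section 5.1 adds: "This is an open-label interventional study". The three analysis groups differ by hyperuricemia, gout and urate-lowering therapy, not by exposure to vitamin C.

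Section 3.2 names as a secondary outcome "Change in taxonomic and functional patterns of gut microbiota post-administration of vitamin C". Section 15.3 analyses it before against after: "Overall differences in microbiome composition from baseline to week 8 will be compared using three principle axes of variation in the microbiome". For single taxa it says: "A linear regression will be analyzed with a bacterial taxon as dependent and host factors as independent variables". It does not list the host factors.

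For the baseline sample, section 5.2 says that participants are "given stool collection kits to take home with them for 2 consecutive days" and return the samples when it suits them. The same section takes a medication history that includes probiotics at Visit 1, repeats it at Visit 2, and asks about medication changes at weeks 1, 4 and 7. No look-back is stated for that history.

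**The concern.** By excluding these exposures at all, the protocol accepts that they disturb what it wants to measure. The rule as written, however, deals only with the day on which eligibility is checked. Someone on antibiotics at the phone screen can qualify as soon as the last tablet is taken, which is when carry-over may be greatest.

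What is at stake is the secondary microbiome-change outcome. If some baseline stools are disturbed and the microbiome recovers over the next 8 weeks, those participants show a change that has nothing to do with vitamin C. An untreated group would show the same recovery, and a contrast between groups would remove it, but this design has no such group. Where the analyses for Ho2, Ho3 and Ho4 use the baseline stool, the same disturbance adds noise to them.

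**Working it through.** **The rule against the comparison.** Section 8.2 tests exposure at one moment. Section 13.1 has eligibility assessed before the enrollment visit and again at it, and section 5.2 has the stool collected at home after that. A course that ended the day before Visit 1 passes both checks. Sections 3.2 and 15.3 then compare that stool with the week-8 stool, and section 4.1 leaves no untreated participants.

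**Does another section close the gap?** The urate model in section 15.3 adjusts for "age, gender, BMI, renal function, and concomitant medications". That model concerns serum urate, and a finished course is not concomitant. The taxon model could include antibiotic use among its host factors, but only if the date of last use has been recorded. False discovery rate correction deals with multiplicity, not with confounding.

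**Size (illustration).** The protocol states no figure on this point, so there is none to reproduce.

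Inputs from the protocol:
- 180 participants (5.1) and 15% drop-out (15.2): 180 × 0.85 = 153 completers.
- One group of about 60 (5.1): 60 × 0.85 = 51 completers.

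Assumptions, not in the protocol:
- p, the share of recent users: 2%, 5% or 10%. In 153 completers this is about 3, 8 or 15 people.
- d, the average shift from recovery in one microbiome feature, in SD of the change score: 0.5 or 1.
- No true vitamin C effect, and a two-sided one-sample z-test of the mean change in one feature at 5%, before any false discovery rate correction.

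Formulas:
- bias in the mean change: b = p × d
- SD of the change with the mixture: s = √(1 + p(1 − p)d²)
- standardised bias: λ = b√n / s
- false-positive rate: Φ(λ − 1.96) + Φ(−λ − 1.96)

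Example for p = 10%, d = 1, n = 153: b = 0.10; s = √(1 + 0.09) = 1.044; λ = 0.10 × 12.37 / 1.044 = 1.185; rate = Φ(−0.775) + Φ(−3.145) ≈ 0.219 + 0.001 = 0.22.

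| p | d | bias (SD) | rate, n = 153 | rate, n = 51 |
|---|---|---|---|---|
| 2% | 0.5 | 0.010 | 5.2% | 5.1% |
| 2% | 1 | 0.020 | 5.7% | 5.2% |
| 5% | 0.5 | 0.025 | 6.1% | 5.4% |
| 5% | 1 | 0.050 | 9.3% | 6.4% |
| 10% | 0.5 | 0.050 | 9.4% | 6.4% |
| 10% | 1 | 0.100 | 22.0% | 10.5% |

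The standard error of a mean change in 153 people is 1/√153 = 0.081 SD, so the bias runs from 0.010/0.081 = 0.12 to 0.100/0.081 = 1.24 standard errors.

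**Offset.** If a share q takes a course between the two stools and shifts by the same d in the other direction, the net bias is (p − q) × d. It is zero when q = p. The table therefore shows recovery alone.

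**The case against.** The strongest reply has four parts.

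- **Small and assumed.** Neither the share of recent users nor the shift comes from the protocol. If recent users are rare, the distortion is negligible, and in a single group of 51 it stays near 10% even at the top of the range. This stands, and it limits the weight of the point.
- **Not in one direction.** A reader might infer that the bias always favours an apparent recovery. The documents do not support that, since a course taken during the 8 weeks pushes the other way and can offset it in the mean. Individual taxa need not cancel exactly.
- **Partly a matter for the analysis plan.** A reader might fault section 15.3 for naming no antibiotic covariate and no rule for stool pairs exposed between visits. Protocols commonly leave such details to the statistical analysis plan, which is not at hand. The protocol does not say whether such pairs are kept or dropped, so silence is no evidence that they are kept. The eligibility rule is different, because it belongs in the protocol.
- **The data may already exist.** Medication history and medication changes are collected. The questionnaires are supplements that are not shown, and they may ask for dates of last use. If so, a sensitivity analysis is possible, but section 8.2 would still admit people just off a course.

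A look-back would also not make the change attributable to vitamin C, because other causes that vary with time remain in an uncontrolled comparison. It removes one avoidable cause that the protocol already recognises.

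**Conclusion.** The point holds as a modest, cheap improvement to a stated eligibility rule. Section 8.2 admits people who have just finished antibiotics or probiotics, and in this all-treated before-after design their recovery can be mistaken for a vitamin C effect on the microbiome. Under the assumptions above, the false-positive rate for one feature in 153 completers lies between about 5% and about 22%, before any offset from courses taken between visits.

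Three stronger readings are not supported. That recovery *will* be read as a vitamin C effect does not follow, because the number of recent users is unknown. That the gout comparison in Ho3 is confounded would need recent antibiotic use to differ between the groups, and nothing in the documents shows that it does. That the trial's main result is at risk is also wrong, since the primary endpoint is change in serum urate and is not directly affected.

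**What to change.** In section 8.2, change the line to *Current use, or use within a fixed period before the baseline stool, of* antibiotics and probiotic supplements. The team sets the period. The ketogenic diet can stay on its own line under current use. State that people inside the period are deferred, not refused. Ask for the date of last use at the phone screen in section 8.3 and confirm it at Visit 1.

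Optionally, use the medication changes already collected at the calls and Visit 2 for a sensitivity analysis of the microbiome-change outcome that leaves out stool pairs exposed between the visits.

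The cost is one eligibility line and one dated question. The downside is that a small share of participants start some weeks later. The optional analysis would also rest on slightly fewer stool pairs.
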